# Methods

The Action Learning (Revans 1980) and Audit Spiral methodologies (Fraser, Lakhani et al. 1998) will be used to carry out a systematic analysis of the QOC and to identify areas for enhancement in the PEP programme. Donabedian’s taxonomy of QOC on structure, processes and outcomes will be used as the evaluation framework (Donabedian 2005).

Investigators will work together with the PEP programme team to:

1. review and identify the structure process and outcome indicators;
2. define the criterion and set the target standard for each indicator;
3. identify any on-site problems of implementation of the programme;
4. provide interim feedback on QOC of the programme;
5. Identify possible actions for improvements;
6. compare the final results against set standards;
7. make recommendations for future PEP programmes.

A QOC framework will be developed by an iterative process and reconciliation between the investigators and the programme providers. This framework lists out the indicators of the structure (staff, facilities, organization, and management), process (what, when and how care is delivered), and outcomes (clinical outcomes, service utilization and patient reported outcomes) with the required criteria and standard of care to be achieved.

## Subjects

All patients who have been enrolled into the PEP programme will be included in the evaluation on process of care for each audit cycle; whereas all enrolled subjects who have been recruited for more than 12 months in the programme will be included in the evaluation on the clinical outcomes of care for each audit cycle.

To determine a difference of programme performance and impact between group (PEP participants and non-participants). A cohort of all eligible DM patients under care of HA GOPC at 1 Sep 2009 would be included for the monitoring of the changes in clinical and service utilization outcomes from Sep 2009 to Sept 2015.

550 patients who have enrolled into the PEP and 550 who have not taken part in the PEP will be invited in person from the general outpatient clinics by trained research assistants at the beginning of each evaluation cycle to take part in a telephone survey on patient reported outcomes for each cluster and written consent will be obtained (appendix A). All subjects who have given consent to the telephone follow-up survey will be interviewed by telephone within four weeks, at 6, 12, 36 and 60 months from recruitment to answer the SF-12 Health Survey on quality of life (QOL), the patient enablement Instrument, the Global Rating Scale (GRS) change in health, and a structured questionnaire on private service utilization rates.

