**Abstract**

**Objectives:** The aim of this study is to evaluate the quality of care (QOC) of the Hospital Authority’s (HA) patient empowerment programme (PEP) programme using an evidence-based structured and comprehensive evaluation framework to identify areas for quality enhancement.

**Design, Setting and Subjects:** A longitudinal study will be conducted using the Action Learning and Audit Spiral methodologies to measure whether the target standard of care intended by the PEP programme is achieved. Each PEP participating clinic and non-government organization (NGO) will be invited to complete a structured evaluation questionnaire. The data of all patients who have enrolled into the PEP for more than one year will be included in the evaluation on the process and outcomes of care. To determine a difference of programme performance and impact between group (PEP participants and non-participants), cohort study would be adopted. A cohort includes all eligible DM patients under care of HA GOPC at 1 Sep 2009 will be followed up on the clinical outcomes including HbA1c, blood pressure, lipids, and complications rates. To evaluate the effect of PEP on patient-reported outcomes, 550 participants, as well as 550 of those who have not participated in the PEP, will be recruited from each cluster and followed up by telephone to evaluate the effect of the programme on quality of life (QOL), patient enablement, global rating of change in health condition and private service utilization at baseline, 6, 12, 36 and 60 months after enrolment. Data on the process of care will be retrieved from the HA medical records. The cost effectiveness analysis (CEA) by mathematical modeling will be carried out by using cost and clinical outcome data provided by the HA, as well as quality-of-life and private service utilization cost data collected by the telephone surveys.

**Main Outcome Measures:** The primary outcomes are the proportion of participants who have received the planned process of care and achieved the target HbA1c and blood pressure levels.

**Data Analysis:** Descriptive statistics on proportions meeting the QOC criteria will be calculated. The changes in clinical, service, and patient reported outcomes at 6 and 12 months will assessed by paired sample t-test for each audit cycle. The audit cycle will be repeated annually over a period of 5 years.

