# Background

Diabetes mellitus (DM) and hypertension (HT) are major causes of morbidity and among the top 10 causes of deaths in Hong Kong in 2008 (Department of Health 2009). The Hospital Authority (HA) has initiated service improvement through introducing the patient empowerment programme (PEP) to improve the quality of care (QOC) for DM and HT patients. The evaluation on the QOC is an essential part of the programme in order to inform future policy. The Family Medicine Unit (FMU) of the University of Hong Kong (HKU) has been appointed by the HA to carry out the evaluation of the QOC of the programme.

The PEP programme invites non-Government organizations (NGO) with experience in community medical service and education to deliver empowerment sessions to enhance patients’ disease specific knowledge and self-management skills, self-efficacy and lifestyle modification. Eligible patients who are ambulatory, have stable mental and emotional conditions, and follow up at general outpatients clinics (GOPC) and family medicine specialist clinics (FMSC) regularly will be recruited for the PEP programme. Enrolled patients will receive generic and disease specific PEP sessions provided by the NGO. Patients will be excluded if they have severe heart failure, end stage renal failure (ESRF) or advanced eye diseases, are unable to understand or communicate in Chinese language, or refuse to give consent.

Studies have found that patient empowerment programmes are effective, especially those that include active patient involvement (Lorig and Holman 2003), in improving outcomes and are somewhat cost-effective. Although more studies would be needed to determine long-term benefits and the cost-effectiveness in both hard and soft indicators (i.e. health care utilization costs vs. less tangible measures of outcome, including quality of life (QOL) and self efficacy. Two trials in Hong Kong indicated the empowerment approach was applicable to the Hong Kong Chinese population (Chan, Chan et al. 2007; Siu, Chan et al. 2007).

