## Sample size calculation

The sample size for the evaluation on QOL change is estimated to detect a minimally clinically important difference (MCID) in health-related quality of life (HRQOL) studies, which is equivalent to Cohen’s small effect size of 0.3 (Cohen 1988). A sample size of 350 patients in total (175 PEP participants and 175 non-participants) is needed in order to have 80% power and 95% confidence interval estimated by independent t-test to detect a small effect size (Erdfelder, Faul et al. 1996). Therefore, 1100 patients (550 PEP participants and 550 non-participants) will need to be recruited to account for 25% dropouts each follow-up (4 times).

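### Survey controls are defined only by not having joined PEP: eligibility for PEP is not required, and there is no rule for controls who join later

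*Protocol*

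**What the plan says.** Protocol, Subjects: alongside 550 PEP enrollees, "550 who have not taken part in the PEP will be invited in person from the general outpatient clinics". The Abstract gives the same definition: "550 participants, as well as 550 of those who have not participated in the PEP, will be recruited from each cluster". Non-participation is the only condition stated for the control group.

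Two other places set conditions that are not carried over:

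- Background limits PEP to ambulatory patients with stable mental and emotional conditions under regular clinic follow-up. It adds: "Patients will be excluded if they have severe heart failure, end stage renal failure (ESRF) or advanced eye diseases". Inability to communicate in Chinese and refusal of consent are further exclusions.
- The preceding paragraph of Subjects, on the record-based comparison, does carry an eligibility condition: "A cohort of all eligible DM patients under care of HA GOPC at 1 Sep 2009 would be included".

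Survey subjects are interviewed at baseline and at 6, 12, 36 and 60 months. Outcome measures lists the change in SF-12v2 scores as a secondary outcome. Sample size calculation sizes the survey for QOL change between participants and non-participants, "estimated by independent t-test to detect a small effect size".

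**The concern.** A control group should consist of people who could have received the programme. A patient turned away from PEP for severe heart failure, end-stage renal failure or advanced eye disease fits the survey control definition as written, and so does a clinic attender with neither diabetes nor hypertension. Who may be invited is a recruitment rule and belongs in the protocol. It cannot be left to an analysis plan, because eligibility at invitation is hard to reconstruct afterwards.

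The second gap is time. Controls are followed for five years. The programme appears to go on enrolling, since Subjects recruits survey patients at the start of each evaluation cycle and applies a rolling 12-month rule. Nothing says how a control who later enrols is identified, kept, censored or reclassified. The follow-up questionnaire in Appendix D has no question on PEP enrolment, and the record extraction in Data Collection is anonymized.

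At stake is the between-group reading of the patient-reported outcomes. The survey's QOL data also feed the cost-effectiveness model (Data analysis, item 5).

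**Working it through.** **1. The plan's own figures.** Inputs from Sample size calculation: effect 0.3 SD, 80% power, two-sided 5% (from the 95% confidence interval), 1:1 allocation, 25% loss at each of four follow-ups.

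- Normal approximation: n = 2 × (1.960 + 0.842)² / 0.3² = 174.4, so 175 per group, as stated. The exact t-test gives 175.4.
- Recruitment: 175 / 0.75⁴ = 553.1, so 554 per group against the stated 550, which is close enough.
- Retained from 550: 412 at month 6, 309 at month 12, 232 at month 36 and 174 at month 60 (550 × 0.75, × 0.75², × 0.75³, × 0.75⁴).

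These figures are not in dispute and serve as the base below.

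**2. Eligibility, by comparing the texts.**

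| Group | Diagnosis stated | PEP criteria stated |
| --- | --- | --- |
| PEP participants (Background) | DM or HT programme | Yes |
| Record cohort (Subjects) | DM | Yes (eligible patients) |
| Survey controls (Subjects, Abstract) | None | None |

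Let f be the share of controls who could not have entered PEP. For a change outcome, the bias in the group contrast is f × (mean change in eligible controls − mean change in ineligible controls). A constant difference in level is present at baseline and at follow-up, so it cancels. Only a difference in trajectory remains. The documents give neither f nor the trajectories. Patients with severe disease might decline faster, which would favour PEP. Attenders without DM or HT might decline more slowly, which would count against it. No size or sign can be attached.

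**3. Later joiners.** Assumption, since the documents give no figure: a share c of controls joins PEP and gains the full effect. The contrast becomes 0.3 × (1 − c). Power is from the noncentral t, two-sided 5%.

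| c | Contrast (SD) | Power at month 60, 174 per group |
| --- | --- | --- |
| 0% | 0.30 | 80% |
| 10% | 0.27 | 71% |
| 20% | 0.24 | 61% |
| 30% | 0.21 | 50% |

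Earlier waves keep more patients. With c = 30% (0.21 SD), power is 85% at month 6, 74% at month 12 and 62% at month 36. Fewer controls would have joined by then, so 30% is severe for the early waves.

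**The case against.** The strongest defence is contextual. The aim and hypotheses concern DM and HT throughout, and the survey sentence follows directly on the eligible cohort, so survey non-participants can be read as the same kind of patient. Controls are met in person at general outpatient clinics, consent, and answer a telephone survey in Chinese. In practice that covers clinic attendance, consent, language and, largely, being ambulatory. The consent form is not available and may say more about who is invited. This narrows the gap but does not close it: the severe-disease exclusions, mental and emotional stability, and the diagnosis are still not required of controls by the text.

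A reader might infer that controls are sicker and that this creates an apparent PEP benefit. If 10% to 20% of controls were ineligible and scored 0.5 to 1.0 SD lower (assumed), the shift would be 0.05 to 0.20 SD, and the chance of a significant result with no true effect would be 8% to 46% at 174 per group. The arithmetic is right, but it applies only to an unadjusted contrast of score levels. The outcome is change in SF-12, from which a stable gap drops out. Without a diagnosis requirement, controls could equally be healthier.

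A reader might also infer that later enrolment goes unrecorded. Appendix B expects enrolled patients to be recorded in the PPI-PEP system. What is missing is a link to the survey controls and a rule for handling them.

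Three further limits stand. Data analysis item 3 names only clinical and service-utilization outcomes for the PEP-versus-control tests, so the independent t-test for QOL rests on the sample-size section alone, and an analysis plan not shown may specify adjustment. Patient-reported outcomes are secondary. The power figures take 550 per group as the whole sample; Subjects and the Abstract describe recruitment for each cluster, and pooling clusters would soften the loss of power but not the dilution or the selection problem.

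**Conclusion.** The point holds as a flaw in the control definition and in the follow-up of controls. As written, the rule admits survey controls who could never have entered PEP, while the neighbouring cohort is restricted to eligible patients. The text permits this mixing but does not show that it occurred. The resulting bias has unknown direction and size, and for change in SF-12 it depends on differing trajectories.

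The dilution from later joiners has a known direction, towards no difference if PEP works. Its size rests wholly on the assumed 10% to 30% joining with full benefit: a loss of 0.03 to 0.09 SD from the 0.3 SD target, and 9 to 30 percentage points of power at month 60. The two mechanisms may offset or add to each other, so neither a positive nor a null QOL result could be read cleanly. This should be corrected, at a weight suited to a secondary outcome.

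**What to change.** 1. In Subjects, and to match in the Abstract, require that survey controls have DM or HT, meet all PEP inclusion and exclusion criteria at invitation, come from the same clinics and recruitment period as the participants, and are not enrolled in PEP.
2. At each telephone wave, ask whether and when the respondent enrolled in PEP. Alternatively, obtain the date through consented linkage to PPI-PEP; the anonymized CMS extraction cannot supply it.
3. Analyse by PEP status at recruitment, with a sensitivity analysis that censors controls at PEP enrolment.
4. Compare groups on follow-up SF-12 adjusted for baseline SF-12, which is already collected, in place of the unadjusted independent t-test in Sample size calculation. Show the contrast in change scores beside it, because in a non-randomised comparison the two can differ when groups start at different levels. Adjustment does not replace item 1.

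The cost is a screening check at invitation, slightly slower control recruitment, and one added question or a linkage consent. Linkage is the dearer route because it needs identifiable data.

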## Sample size calculation

The sample size for the evaluation on QOL change is estimated to detect a minimally clinically important difference (MCID) in health-related quality of life (HRQOL) studies, which is equivalent to Cohen’s small effect size of 0.3 (Cohen 1988). A sample size of 350 patients in total (175 PEP participants and 175 non-participants) is needed in order to have 80% power and 95% confidence interval estimated by independent t-test to detect a small effect size (Erdfelder, Faul et al. 1996). Therefore, 1100 patients (550 PEP participants and 550 non-participants) will need to be recruited to account for 25% dropouts each follow-up (4 times).

## Data Collection

Evaluation on structure and process

The co-ordinator of each participating clinic and all participating NGO will be asked to complete the structure of care questionnaire (appendix B). Anonymized data will be retrieved from the computerized medical record system (CMS) by the HA Statistics team to determine the patient recruitment rate, enrollment rate, attendance rate, compliance with assessment as per protocol, number of investigations and referral rate.

Evaluation on outcomes of care

Anonymized data on HbA1c, blood pressure (BP), low-density lipoprotein (LDL), body mass index (BMI) and annual attendance rates for GOPC, specialist outpatient clinic (SOPC) , accident and emergency (A&E) and hospital attendance rates, patient knowledge on disease at baseline and 12 months will be retrieved from the CMS by the HA Statistics team. The audit cycle will be repeated annually over a period of 5 years. This data will be extracted are shown in the data collection form in appendix C.

The 550 patients in the PEP programme who are willing to take part in the telephone survey will be contacted by a trained research assistant who will obtain verbal consent from each patient. Each patient will then answer the Chinese (Hong Kong) Short Form-12 version 2 (SF-12v2) Health Survey within one month from enrolment, and then at 6, 12, 36 and 60 months to repeat the SF-12v2 together with the Patient Enablement Instrument (PEI), Global Rating Scale (GRS) of change in health condition and private service utilization (appendix D).

- 1. The Chinese (Hong Kong) Short Form-12 version 2 (SF-12v2) Health Survey is a generic measure HR QOL. It has been validated and normed on the general Chinese population in Hong Kong (Lam, Wong et al. 2010). It measures eight domains on physical functioning, role physical, bodily pain, general health, vitality, social functioning, role emotional and mental health on a scale range from 0 to 100. A higher score indicates better HRQOL. The eight domain scores can be summarized into two summary scores, the physical (PCS) and mental (MCS) component summary.
  2. The Patient Enablement Instrument (PEI) is a measure of patient’s enablement in coping with the illness and life (Howie, Heaney et al. 1998). It has 6 items each rated on a 3-point (0, 1, and 2) scale. The summation of the item scores gives the PEI score with a higher score indicating better enablement. The PEI has been translated into Chinese and shown to be valid and reliable in the general Chinese population (Lam, Yuen et al. 2010).
  3. The Global Rating Scale (GRS) is adapted from those used in studies by Jaeschke and Osoba et al (Jaeschke, Singer et al. 1989; Osoba, Rodrigues et al. 1998). It assesses the subject’s subject global perception of any change in the overall health condition on a 7-point scale (-3, -2, -1, 0, 1, 2, and 3) over the six months.

## Outcome measures

**Primary**

- The proportion of clinics/NGO that have satisfied each of the set structure criteria.
- The proportion of patients who have complied with the criterion process of care.
- The proportion of DM patients who have achieved a HbA1c level <7%.
- The proportion of HT/ DM patients who have achieved the target blood pressure.
- The estimated 10-year cardiovascular disease risk.

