## Hypotheses

The following hypotheses will be tested:

1. The criteria on structure and process should be achieved by all participating clinics and NGO;
2. More patients with DM will achieve the target HbA1c after 12, 24, 36 and 48 months in the PEP programme;
3. More patients with HT or DM will achieve the target blood pressure levels after 12, 24, 36 and 48 months in the PEP programme;
4. In longer terms, HT/ DM patients will have reduced cardiovascular risks and fewer complications;
5. Patients should report an improvement in quality of life (QOL), enablement and overall health condition after the PEP programme;
6. Patients who take part in PEP programme should not have any increase in service utilization rates.

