## Data analysis

1. Descriptive statistics on standard of care will be calculated, including percentage of centers meeting each structure criterion, percentage of subjects enrolled, dropped out, completion of the programme, receiving criterion process, investigations and referral per protocol, and percentage of subjects achieving the criterion outcome.
2. The change in clinical, service, and patient reported outcomes after the PEP programme at baseline, 6, 12, 36 and 60 months will be compared by paired sample t-test. The audit cycle will be repeated annually over a period of 5 years.
3. Independent sample t-test or Chi square test as appropriate will be used to compare the clinical and service utilization outcomes between PEP patients and controls.
4. Independent sample t-test or Chi square test as appropriate will be used to compare the clinical and service utilization outcomes between results in achieved in different audit cycles.
5. Cost effectiveness analysis (CEA) by mathematical modeling will be carried out by using cost and clinical outcome data provided by the HA, as well as quality-of-life and private service utilization cost data collected by the telephone surveys.

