**Patients require special treatment:**

| **Data Required** | **Number of  patients** | **Time (in days) from problem recognition** |
| --- | --- | --- |
|
| Identified to have problem being given treatments per protocol |  |  |
| Referred for additional service |  |  |
| Refused additional service |  |  |

| **Time (Month)** | **Data required** |
| --- | --- |
| 0, 12, 24, 36 and 48 | **Clinical data** |
| HbA1c |
| Systolic BP |
| Diastolic BP |
| BMI |
| LDL-C |
| **Service utilization** (in the past 12 months) |
| Number of hospitalization |
| Number of A&E attendance |
| Number of GOPC consultation |
| Number of SOPC consultation |
| 0 and 6 months | **Patient reported** |
| Disease knowledge score |
| QoL score |
| PEI* |
| GRS* |

BP = Blood Pressure; BMI = Body Mass Index; LDL-C = Low density Lipoprotein Cholesterol; GOPC = General Outpatient Clinic; SOPC = Specialist Outpatient Clinic; KAP = Knowledge, Attitude and Practice.

*Measured at 6 months only.

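### The uncontrolled paired test of 10-year cardiovascular risk mixes ageing with programme effect at 36 to 48 months, if the unnamed score uses attained age

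*Protocol*

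**What the plan says.** The Protocol's Outcome measures section lists "The estimated 10-year cardiovascular disease risk" as a primary outcome. It names no equation and gives no rule for re-scoring a patient at follow-up.

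Hypothesis 4 expects a fall over time and names no comparator: "In longer terms, HT/ DM patients will have reduced cardiovascular risks and fewer complications".

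Data analysis item 2 says that change in clinical, service and patient-reported outcomes "after the PEP programme at baseline, 6, 12, 36 and 60 months will be compared by paired sample t-test". Item 3 adds an independent-sample t-test or chi-square test to "compare the clinical and service utilization outcomes between PEP patients and controls". The cohort that Subjects describes for the participant versus non-participant comparison is "A cohort of all eligible DM patients under care of HA GOPC at 1 Sep 2009", followed from September 2009 to September 2015.

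The time points differ between sections. Appendix C schedules clinical data at months "0, 12, 24, 36 and 48", and hypotheses 2 and 3 also stop at 48 months. The Abstract mentions paired tests of change at 6 and 12 months only.

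**The concern.** A 10-year cardiovascular risk score is a calculated quantity in which age is ordinarily an input. Re-score the same patient three or four years later with identical HbA1c, blood pressure, lipids, BMI and smoking, and the value is higher. The paired difference then estimates programme effect plus ageing, and ageing works against the direction of hypothesis 4. The two other patient-level clinical primary outcomes, HbA1c below 7% and blood pressure at target, do not have this feature, because age is not part of the quantity measured.

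At stake is the reading of one primary outcome in a study meant to guide policy. A programme that modestly improved risk factors could appear in the before-after result as having had no effect or having made patients worse. The clinical evaluation takes in all patients enrolled for more than 12 months, so even a small systematic shift is likely to be statistically significant.

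**Working it through.** **The plan's own figures.** The Protocol gives no effect size, variance or sample size for cardiovascular risk. Its one calculation is for quality of life: an effect "equivalent to Cohen’s small effect size of 0.3" with "80% power and 95% confidence interval estimated by independent t-test". That reproduces (175 per group; 175/0.75⁴ = 553 after four rounds of 25% dropout, against 550 stated) but has no bearing here.

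**Inputs.** From the Protocol: the outcome, the paired test and the follow-up times. Assumed, because the Protocol is silent: that the score uses attained age, how steeply it rises with age, and the baseline risk.

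**Check 1: relative drift in the score.** With every modifiable factor unchanged, R(t) = R(0) × (1 + r)^t. Take R(0) = 15% and r = 4% to 8% per year.

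| Months | Multiplier | Score | Rise in points |
| --- | --- | --- | --- |
| 12 | 1.04 to 1.08 | 15.6% to 16.2% | 0.6 to 1.2 |
| 36 | 1.125 to 1.260 | 16.9% to 18.9% | 1.9 to 3.9 |
| 48 | 1.170 to 1.360 | 17.5% to 20.4% | 2.5 to 5.4 |
| 60, if clinical data are collected then | 1.217 to 1.469 | 18.2% to 22.0% | 3.2 to 7.0 |

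**Check 2: can drift hide a real improvement?** Let ageing act on the underlying hazard at rate g per year, over a wider range of 2% to 8%, and let k be the hazard ratio from better risk factors: R(t) = 1 − (1 − R(0))^(k(1 + g)^t). Take R(0) = 20% and a 10% improvement, k = 0.9. Without ageing the score would fall to 1 − 0.8^0.9 = 18.2%. With ageing:

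| g per year | 12 months | 36 months | 48 months | 60 months |
| --- | --- | --- | --- | --- |
| 2% | 18.5% | 19.2% | 19.5% | 19.9% |
| 3% | 18.7% | 19.7% | 20.2% | 20.8% |
| 5% | 19.0% | 20.7% | 21.7% | 22.6% |
| 8% | 19.5% | 22.4% | 23.9% | 25.6% |

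At 12 months the improvement still shows as a fall throughout the range. At 48 months it shows as a rise for g of 3% or more. At 2% it remains a fall at 48 months, and the drift roughly offsets it by 60.

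**Check 3: break-even.** For the paired test to show no change, risk factors must cut the hazard by 1 − (1 + g)^(−t). For g from 2% to 8% this is 5.8% to 20.6% at 36 months, 7.6% to 26.5% at 48 and 9.4% to 31.9% at 60.

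**Check 4: would drift alone reach significance?** Take a drift of 2.6 points, within the 36- and 48-month ranges of check 1, an assumed SD of change of 10 points, and only 174 patients. The probability is about Φ(2.6/(10/√174) − 1.96) = Φ(1.47) = 93%. With all enrolled patients analysed it would probably be higher.

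**The case against.** The strongest reply is that item 3 already supplies a control. Ageing common to participants and non-participants cancels in that comparison, and the Protocol assigns the question of programme impact to that cohort. This stands, and it sets the scope: the flaw does not reach every analysis of this outcome. What remains is that item 3 is unadjusted, that its described cohort is diabetic patients only, and that item 2 is a separate test with no comparator. Patients with hypertension alone have no described control for ageing.

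A second reply is that item 2 does not name the score, and that the Protocol's lists of clinical data do not include it. Treating it as one of the clinical outcomes in item 2 is an inference, though a natural one for a primary outcome that hypothesis 4 expects to change.

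Third, the equation and the rule for follow-up scores may be in an SAP that is not shown. That is fair as to the derivation. The point here is the combination that the Protocol does fix: this outcome, an uncontrolled paired test and long follow-up.

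Fourth, the 60-month horizon is weakly supported. The 6, 12, 36 and 60-month schedule is that of the telephone survey, and Appendix C stops clinical data at 48 months. The point therefore rests on 36 to 48 months.

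A reader might go further and infer two things that the documents do not support. One is that hypothesis 4 would be rejected because of ageing: the hypothesis names neither a test nor a comparator, and item 3 can also address it. The other is that comparisons between audit cycles (item 4) must drift upward: new entrants join each cycle, so later cycles need not be older.

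**Conclusion.** The point holds for the uncontrolled within-patient comparison of 10-year risk at 36 to 48 months, and at 60 months if clinical data are collected then. It rests on one assumption from outside the document, that the unnamed score uses attained age. Given that, the upward direction of the drift does not depend on the values chosen, but its size does: from 15%, about 1.9 to 3.9 points at 36 months and 2.5 to 5.4 at 48 months under a 4% to 8% relative rise per year.

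Whether a real improvement is masked depends on its size relative to the break-even. A 10% hazard reduction is outweighed at 48 months for hazard growth of 3% per year or more, but not at 2%. At 12 months the problem is minor. The comparison with controls is not subject to the common ageing drift, though it is unadjusted and described for diabetic patients only.

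**What to change.** For the within-patient test, compute follow-up risk with age, and diabetes duration if the equation uses it, held at the baseline value. Label the result as change in risk factors. Interpret attained-age risk only as the difference between participants and non-participants in change from baseline over the same interval. Name the equation, and reconcile the 60-month point in Data analysis item 2 with the 48-month limit in Appendix C.

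The cost is a sentence or two in the outcome and analysis sections and one derived variable, with no data beyond what the score already needs. The downside is that an age-fixed score is not the patient's current absolute risk and must not be reported as such. Making the between-group difference in change the main test of this outcome would also remove the common drift, but for patients with hypertension alone it would need a comparison group that the Protocol does not now describe.
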